## Patient selection criteria

General PSM patient selection criteria will include 1) medical stability at the time of PSM initiation; 2) cognitive stability and capable of following instructions and/or has a willing and capable caregiver; and 3) currently self-testing with a home INR device. Specific PSM patient selection criteria related to participation in the PSM implementation study will include 1) goal INR range of 2.0 to 3.0 or 2.5 to 3.5; 2) completed more than 9 months of warfarin therapy at time of enrollment; 3) willing to use single warfarin tablet strength; 4) planned duration of warfarin therapy of at least 6 months; 5) willing to test INR every 7-14 days; 6) receiving majority of care within the enrolling site's healthcare system; and 7) able to maintain internet access throughout study participation.

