#### *Implementation (Fidelity)*

Self-reported INR values measured during the 6-month follow up period will be individually assessed for fidelity to key PSM elements as described below. For enrolled participants actively engaged in PSM, the percentage of INRs independently and appropriately managed by the participant (i.e., participant used INR to determine warfarin dosing plan while neither contacting a clinician nor taking actions deemed inappropriate by clinicians) will be calculated. Adherence to key PSM elements will be categorized as adherent or nonadherent for each INR. Data for this outcome will be censored on the date of PSM failure or the study end-date, whichever comes first. INRs tested within  $\pm 3$  days of the date specified by PSM

participants will be categorized as fully adherent and INRs measured >3 days before or after as nonadherent. Adherence to warfarin dose selection recommendations as specified by the My Warfarin online decision support tool will be evaluated for each INR. Warfarin doses within  $\pm 5\%$  of the specified dose recommendation based on the INR result will be considered adherent.

For “implementation” outcomes, the percentage of INRs falling into adherent and nonadherent categories will be calculated for each patient using the total number of INRs performed during the PSM phase as the denominator. The mean (standard deviation) percentages for each adherence category will be summarized, stratified by implementation site, and compared using ANOVA. An omnibus P-value  $< 0.05$  will be considered statistically significant and multiple comparison tests used to determine if significant differences exist between specific sites if needed.

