| 5. Value of INR being reported?                                                                     | -Patient enters INR value                                                                                                                                                                                             | If INR is 5.0 or higher, patient instructed to contact their anticoagulation provider                                                                                                       |
| 6. Based on your INR value, do you plan on adjusting your weekly warfarin dose?                     | -Yes
-No                                                                                                                                                                                                           | If "No" survey skips to question 20                                                                                                                                                         |
| 7. In response to this INR, who ultimately decided the new warfarin dose you will take?             | -I did
-Someone else/healthcare provider
-Other                                                                                                                                                                 | If "I did", question 8 is asked; otherwise, survey skips to question 9                                                                                                                      |
| 8. How did you decide which warfarin dose to take?                                                  | -My warfarin website tool
-My own decision
-Other                                                                                                                                                               |                                                                                                                                                                                             |

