| 9. Over the past week what tablet strength of warfarin did you use?                                 | -1 mg (pink)
-2 mg (lavender)
-2.5 mg (green)
-3 mg (tan)
-4 mg (blue)
-5 mg (peach)
-6 mg (teal)
-7.5 mg (yellow)
-10 mg (white)
-I used different tablet strengths (more than one color) |                                                                                                                                                                                             |
| 10. Over the PAST week, how many tablets did you actually take each day (enter 0 for missed doses)? | -Patient fills in a grid with the number of tablets taken each day                                                                                                                                                    | Dates for the grid will auto populate based on the INR date entered for question 4
Total milligrams taken over the previous week automatically calculate from values entered in the grid |
| 11. Since your last INR, which of the following changes have occurred?                              | -Bleeding symptoms
-Clotting symptoms
-New or worsening illness                                                                                                                                                 | If "Bleeding symptoms" question 12 is asked                                                                                                                                                 |

|                                                                         |                                                                                                                                                                                                                                                                                                                                                                                                                                      |                                                                                                                                                                                                                                                                                     |

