|                                                                                                                                                 |                                                                          |                                                                                                          |
|-------------------------------------------------------------------------------------------------------------------------------------------------|--------------------------------------------------------------------------|----------------------------------------------------------------------------------------------------------|
| supplements) (select all that apply)?                                                                                                           | -Other                                                                   |                                                                                                          |
| 16. What changes in diet/vitamin K intake (e.g., green leafy vegetables, vegetable smoothies, nutrition, or vitamin supplements with vitamin K) | -INCREASED vitamin K intake
-DECREASED vitamin K intake
-Other     |                                                                                                          |
| 17. Did you contact your anticoagulation management service provider regarding these symptoms?                                                  | -Yes
-No                                                              |                                                                                                          |
| 18. Did you already take your warfarin dose for today before checking your INR?                                                                 | -Yes
-No                                                              | Used to auto-populate dates of the grid for question 19                                                  |
| 19. Over the NEXT week, how many tablets do you plan on taking each day?                                                                        | -Patient fills in a grid with the planned number of tablets for each day | Total milligrams to be taken over the next week automatically calculated from values entered in the grid |

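### The per-INR survey records tablet strength for the past week only, so the planned weekly milligrams can be wrong when strength changes and cannot be calculated when strengths are mixed

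*Protocol*

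**What the plan says.** The survey table in the protocol's Supplementary material collects dose as tablet counts plus a strength.

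- Question 6 asks whether the weekly dose will be adjusted. A No answer skips to question 20, so questions 7 to 19 belong to reports that plan a change.
- Question 9 asks "Over the past week what tablet strength of warfarin did you use". The answers are nine single strengths from 1 to 10 mg, or "I used different tablet strengths (more than one color".
- Question 10 is a daily grid of tablets taken in the past week: "Total milligrams taken over the previous week automatically calculate from values entered in the grid".
- Question 19 asks "Over the NEXT week, how many tablets do you plan on taking each day", with the comment "Total milligrams to be taken over the next week automatically calculated from values entered in the grid".

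Three other places bear on this. Patient selection criteria asks that participants be "willing to use single warfarin tablet strength". Implementation (Fidelity) compares doses with the My Warfarin recommendation, and those within ±5% "of the specified dose recommendation based on the INR result will be considered adherent". The section on documenting PSM activities in the EHR has a survey summary emailed to the site team, and Figure 1 lists remote clinician review of dosing decisions as a core element.

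**The concern.** Tablet counts become milligrams only when multiplied by a strength. For the coming week the printed form asks for counts but not strength. The only strength it holds describes the week just ended. A patient who changes the dose by moving to a different tablet would then have next week's counts multiplied by last week's strength.

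The mixed-strength answer is a second gap. It carries no milligram value, and no printed item asks which strengths were used or how many tablets of each. Both totals then lack a multiplier, although the form says both are calculated automatically.

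At stake is the accuracy of the recorded planned dose at reports where a dosing decision has just been made. That record is available for clinician review and is the only planned-dose field shown that could feed the ±5% measure. A strength that was never collected cannot be supplied by the analysis.

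**Working it through.** The plan states no figure here to reproduce. The check reads the form item by item and then sizes the error.

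**Inputs**
- Strengths listed in question 9: 1, 2, 2.5, 3, 4, 5, 6, 7.5 and 10 mg.
- Tolerance: ±5%, from Implementation (Fidelity).
- Assumption: question 9 supplies the multiplier for question 19. It is the only strength item on the form. The other strengths the protocol mentions, at screening (Table 2) and at invitation (Adoption), are older still.
- Illustration only: 7 tablets a week.

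**Step 1. When a total exists.** Question 19 is reached only if question 6 is answered Yes. A change of strength with no change in weekly dose, for example at a refill, produces no question 19 total.

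**Step 2. Strength unchanged.** Recorded total = count × strength = planned total. The error is 0%.

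**Step 3. Strength changed.** Recorded total = n × s_old and planned total = n × s_new, so the relative error is s_old / s_new − 1. The tablet count n cancels.

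| Change | Recorded | Planned | Error |
|---|---|---|---|
| 5 to 6 mg | 7 × 5 = 35 mg | 7 × 6 = 42 mg | 5/6 − 1 = −16.7% |
| 5 to 4 mg | 35 mg | 7 × 4 = 28 mg | 5/4 − 1 = +25% |
| 5 to 2.5 mg | 35 mg | 7 × 2.5 = 17.5 mg | 5/2.5 − 1 = +100% |

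Nine strengths give 9 × 8 = 72 ordered pairs, and all 72 have an absolute error above 5%. The smallest is 16.7% (2.5 to 3 mg, or 5 to 6 mg). The smallest overstatement is 20% (3 to 2.5 mg, or 6 to 5 mg).

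**Step 4. Against the tolerance, if question 19 is the dose compared.** The ratios s_old / s_new nearest to 1 are 0.833 and 1.20. A plan truly between 0.95 and 1.05 of the recommendation would be recorded at no more than 1.05 × 0.833 = 0.875, or at no less than 0.95 × 1.20 = 1.14. Both lie outside 0.95 to 1.05. So every truly adherent plan that involves a change of strength would be scored nonadherent. By the same ratios, any such report scored adherent would truly be outside the tolerance.

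**Step 5. Mixed strengths.** Take 7 whole tablets in the past week with at least one 2.5 mg and one 5 mg tablet. The total could be anything from 6 × 2.5 + 5 = 20 mg to 6 × 5 + 2.5 = 32.5 mg. For the coming week, when the patient may use either strength or both, it could be from 7 × 2.5 = 17.5 mg to 7 × 5 = 35 mg. The counts alone do not determine either total.

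**Step 6. Later correction.** The next report shows the new strength only if it too plans a dose change. Otherwise question 6 skips past questions 9 and 10.

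**The case against.** The strongest reply is that the problem is narrow and partly inferred.

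- *The multiplier is not named.* The comments say only that milligrams come from the grid, and a summary table may omit calculated or branching fields. This stands: the Step 3 error is conditional on question 9 being used.
- *Participants are selected for willingness to use one strength.* The usual adjustment is then a different number of the same tablets, and the total is exact. This limits how often the error arises. It does not remove it, because the criterion concerns willingness at selection, does not exclude moving from one single strength to another, and the form itself provides for a mixed answer.
- *The downstream links are not stated.* The protocol does not say that question 19 is the dose used for the ±5% measure, nor what the emailed summary contains. Site staff may see the strength, the daily counts and any free-text comment. This also stands.

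A reader might infer that planned dose is wrong at every dose-change report, or that a refill in a new strength corrupts the record. Steps 1 and 2 show otherwise. A reader might also see a contradiction between the selection criterion and the mixed-strength answer. There is none, since a form may record exceptions to what patients said they were willing to do.

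**Conclusion.** The point holds as a minor data-capture gap. On the printed form, strength is asked only for the past week, while next week's counts are converted to milligrams. If question 9 is the multiplier, the planned weekly total is wrong by at least 16.7% at dose-change reports where the strength also changes. After a mixed-strength answer, neither total can be calculated, whichever multiplier was intended, unless the form has fields that are not printed.

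The number of affected reports is unknown. The protocol does not say how often strengths change, and the selection criterion suggests seldom. The effect is confined to the recorded planned dose available for clinician review and, if question 19 feeds it, to the ±5% dose-adherence measure.

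It would go too far to read this as a threat to the main results. The primary outcome is completion of 6 months of PSM, and time in therapeutic range rests on INR values. Neither uses planned milligrams. Nor do the documents show that the site team would be misled about any patient's dose.

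**What to change.** 1. Within the branch where question 6 is Yes, add one item before question 19 asking which tablet strength will be taken over the next week, and calculate the question 19 total from it. With the strength recorded, the mismatch error is 0%.
2. When more than one strength is reported for either week, open one row of counts per strength in the matching grid (question 10 or 19).
3. For records already collected (enrollment began March 1, 2023), treat the milligram total as missing where mixed strengths were reported. Where a later report shows a different strength, check the earlier planned total against the chart.
4. If the live form already handles these cases through fields not printed, state which strength question 19 uses and how mixed answers are treated.

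The cost is a REDCap edit: one short extra item at dose-change reports only, plus a branching rule, with no added visits. The drawback is a difference in form version between earlier and later records, which should be noted in the data documentation. The change concerns data capture only and proposes no dose or clinical rule.
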